**Figure 4 figure4:**
[figure not shown]
Virtual reality (VR) mirror therapy: (A) screenshot of the apple-picking task from the perspective of a participant and (B) a patient performing the VR mirror therapy.

##### Teledance

This small-scale pilot study will be conducted by UQAM-CRIR in Canada. The objective is to test the teledance intervention, including a series of video vignettes adapted for stroke rehabilitation and follow-up modalities with users (asynchronous and synchronous). To do so, the intervention will be subject to a formative evaluation by the users to identify and resolve problems that may influence their experience [61] and to explore its potential impacts. By testing the intervention within an intensive functional rehabilitation setting, the objective is to identify the characteristics of users to whom such an intervention can be applied, evaluate its usability and safety, and explore its potential impacts. Data will be collected during each intervention session and at the end of the study.

Participants will include 9 clinicians (eg, physiotherapists, occupational therapists, and speech language therapists), 15 patients with stroke, and their relatives (N=15, comprising spouses, adult family members, or caregivers) recruited from 3 rehabilitation sites in Montreal, Canada. Included clinicians are required to have at least one year of work experience in a stroke rehabilitation program. The inclusion criteria for patients include the following: new admission to the facility’s stroke program (≤14 days) and ability to participate safely and independently following an initial assisted teledance session with a clinician (or with the sustained assistance of a relative). Patients who are aggressive or have known symptoms of dementia and Alzheimer disease before the stroke and who do not have sufficient cognitive abilities to follow instructions and give informed consent will be excluded. Relatives will include spouses, adult family members, or caregivers who are in close contact with the patient during rehabilitation. All participants must be able to understand and express themselves in French.

The teledance intervention will be offered to patients during their stay in the hospital and will consist of video vignettes delivered via the OpenTera software platform [62] on a digital tablet (eg, iPad), as well as follow-up modalities offered via OpenTera or other means. The intervention will be conducted by 2 dance educators for 5 to 6 weeks. Video vignettes will be +20 to −20 minutes long and offer thematic content, which will be performed in a sitting or standing position and either alone or assisted. Patients will be instructed to perform teledance at least 6 times per week for approximately 2 hours of dance per week. Follow-up sessions (patient-clinician, patient-dance educator, or clinician-dance educator) will also be included.

##### Augmented Gait Training

This small-scale pilot study (WALKAGAIN) will be conducted by McGILL-UdeM-CRIR in Canada. The main objective of this pilot study is to assess the effect of adding augmented gait training to usual rehabilitation and technology targeting the walking abilities of individuals admitted to rehabilitation after stroke in single-tasking, dual-tasking, and multitasking conditions. A secondary objective is to establish an international common data set for standing mobility assessment and conceptualize the common elements (dose, progression, etc) of the training protocols to be able to compare data among sites or analyze them together. To do so, a before-after pragmatic design with a blind outcome assessment will be set up to assess the performance of participants using augmented training protocols as compared with a control group or previously collected data (if available). The data from two Montreal Metropolitan (Canada) rehabilitation sites (Jewish Rehabilitation Hospital and Institut de réadaptation Gingras-Lindsay-de-Montréal) will be pooled together to assess the overall effect of the concepts of augmented gait training. Standardized outcomes will be collected in the week before and week after the locomotor training. We will also implement a follow-up assessment at 6 months (telephone call).

A total of 12 to 15 patients with stroke will be recruited from the stroke unit of the 2 sites for each locomotor training protocol. Participants will be selected for their potential to improve gait capacities and according to the requirements of their individual goals for improvement. The inclusion criteria will be the following: (1) having a first unilateral stroke and being in rehabilitation, (2) having initiated the gait training with or without assistive devices, (3) tolerating 1 hour of exercise with breaks, (4) in the presence of aphasia showing no more than mild or mild to moderate impairment, (5) having a reliable yes and no. The exclusion criteria will include cerebellar lesions, major pain, hemineglect or hemianopsia, signs of major depression quantified with a score of ≥10 out of 15 on the Geriatric Depression Scale [63], severe cognitive deficits defined with a score of <25 out of 30 on the Mini-Mental State Examination developed by Folstein et al [64], cardiorespiratory problems, and other medical and cognitive conditions that could affect the ability to understand instructions, as verified by medical records. We will also collect data on usability, feasibility, and opinions from clinicians about the training interventions through questionnaires or interviews.

Three major technologies (either individually or combined) will be used for locomotor training: biomechanical (eg, split belt training, walking with loaded segment, ascending slope), haptic (eg, vibrations), and VR (virtual environment), as shown in Figure 5. The precise locomotor training protocol will be decided by the clinicians in consultation with the researchers and will take into consideration the preferences of the participants (after phase 1). All locomotor training will include cognitive or language tasks as well attention-demanding tasks, implemented gradually from simple to more complex (single tasking, dual tasking, and multitasking) while the gait training will also be progressed. The training will consist of, for example, 30 minutes of walking or doing a number of steps, using the selected protocol with 5 minutes of warming-up and 5 minutes of recovery. Participants will be allowed to take breaks if their heart rate exceeds 60% of their maximal heart rate or they reported an exertion of 5 on the Borg rating scale, which represents severe exertion [65]. The training will be restarted when the participant’s heart rate will lower back to its level at rest. The augmented gait training will be given twice a week for 10 sessions (5 weeks). Before each training session, the participant’s heart rate (eg, Polar Electro Oy) and blood pressure will be taken at rest. The age-related maximum heart rate will be calculated using the Karvonen formula [66].

**Figure 5 figure5:**
[figure not shown]
Examples of technologies for augmented gait training: (A) split-belt training (biomechanics), (B) vibrations (haptic), and (C) virtual reality.

#### Harmonization (Phase 3)

To define harmonized protocols and procedures (eg, for patient screening=outcomes and outcome measures) for living lab research in the context of technology in rehabilitation, the consensus process will involve a modified Delphi methodology (web-based, 3-round Delphi survey) followed by a consensus meeting of the living labs. The Delphi technique is a method for reaching consensus comprised of sequential questionnaires answered anonymously by a panel of experts with feedback provided after each questionnaire round [67,68]. A preliminary list of items for the Delphi survey will be based on literature research and findings of phases 1 and 2. For each living lab, 2 researchers participated (N=12).

### Data Analysis

#### Cocreation (Phase 1)

Best practices for content analysis will be exchanged among partners to ensure a harmonized approach and the generalizability of the findings. Subsequently, for each test site, one or more researchers trained in qualitative methodology will provide a written report of each cocreation workshop and will use content analysis to analyze the data using main themes and subthemes.

#### Small-Scale Pilot Studies (Phase 2)

Best practices for analyses will be exchanged among partners to ensure a harmonized approach and the generalizability of the findings. However, for each small-scale pilot study, the statistical approach might vary according to the needs of the respective study. In general, descriptive statistics will be presented for demographic information. For quantitative data, normal distribution will be tested. The effects of an intervention on dependent variables will be assessed over time (eg, before-after, follow-up sessions) using repeated-measures parametric or nonparametric tests. The effect sizes of changes found among evaluations will be computed. The significance level is set at *P*<.05.

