##### Short-Arm Human Centrifuge

This small-scale pilot study will be conducted by AUTH in Greece. In this pilot study, the SAHC is used for physical and cognitive rehabilitation to mitigate the detrimental effects of bed rest [20,57] (Figure 2). The objective is to assess the combined effects of artificial gravity and physical activity compared with standard of care in patients with stroke (acute or chronic) and healthy older adults over a period of 3 months (1 hour per session, 3 sessions per week). Participants will be assigned randomly to the SAHC training, standard of care training, or passive control. Data will be collected across the domains of body structure and function, activity, and participation as classified by the World Health Organization International Classification of Functioning, disability, and health, at six time points: at baseline, 4 weeks, 8 weeks, 3 months, and 6- and 12-month follow-ups.

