**Figure 2 figure2:**
[figure not shown]
Short-arm human centrifuge.

Participants will include 30 patients with acute stroke (15 SAHC and 15 passive control) and 30 patients with chronic stroke (15 SAHC and 15 passive control). They will be recruited from the Euromedica-Arogi Rehabilitation Center in Thessaloniki, Greece. The inclusion criteria include the following: individuals aged 18 to 70 years, without psychiatric disorder, without vertigo, without nausea or chronic pain, and without a history of syncope. The exclusion criteria include the following: individuals with a height >2 m, elite athletes, individuals with chronic use of substances (drugs or alcohol), individuals who have had a recent surgery, individuals with current arrhythmias, individuals with severe migraines, pregnant individuals, individuals with epilepsy, individuals with cholelithiasis or kidney stones, individuals with recent wounds from surgery, individuals with recent fractures, individuals with acute inflammation or pain, individuals with newly inserted metal pins or plates, and individuals with newly implanted stents.

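### Centrifuge pilot: the default repeated-measures tests, if applied, give a less precise arm comparison than one adjusted for baseline (and for stroke phase, if phases are combined)

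*Protocol article*

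**What the plan says.** The protocol article, Data Analysis, Small-Scale Pilot Studies (Phase 2), covers all six pilots in one paragraph. It allows that "for each small-scale pilot study, the statistical approach might vary according to the needs of the respective study". It then gives a general default: effects on dependent variables are assessed over time "using repeated-measures parametric or nonparametric tests", effect sizes of changes are computed, and "The significance level is set at *P*<.05".

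The Short-Arm Human Centrifuge section gives the design to which this default would apply. Outcomes are taken "at six time points: at baseline, 4 weeks, 8 weeks, 3 months, and 6- and 12-month follow-ups", so baseline is one of the repeated measurements. The planned numbers are "30 patients with acute stroke (15 SAHC and 15 passive control) and 30 patients with chronic stroke (15 SAHC and 15 passive control"). On allocation the same section says: "Participants will be assigned randomly to the SAHC training, standard of care training, or passive control". It names no method of its own for comparing arms.

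**The concern.** The pilot is randomised and has a comparative aim, so the quantity of interest is a difference between arms after baseline. When baseline is one of the repeated levels, the arm-by-time contrast between baseline and a later visit is a comparison of mean changes. With baseline as a covariate, the same contrast has a smaller or equal error variance in large samples. The usual rank tests for repeated measurements (Friedman, Wilcoxon signed-rank) carry neither a baseline covariate nor a phase term.

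The planned numbers are also equal across arms within acute and within chronic stroke. If the two phases were put into one analysis without a phase term, and patients in one phase changed more than in the other, that difference would go into the residual. The arm estimate would stay unbiased, but its interval would be wider than the design allows.

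At stake is precision in a small study that still intends to test at 5% and report effect sizes.

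**Working it through.** **Inputs from the article.** 15 + 15 = 30 patients in each phase and 30 + 30 = 60 in total, so 30 per arm if the phases are combined. Baseline is measured. The level is 0.05; sidedness is not given, so two-sided is assumed. The article gives no power, effect size, SD or correlation for this pilot, so there is no figure of its own to reproduce.

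**Assumptions.** Equal SD at baseline and follow-up, set to 1; one post-baseline visit compared with baseline; correlation rho between the two; D, the acute-chronic difference in mean change, in SDs of change. All are varied because the article gives none.

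**Step 1: baseline as a repeated level or as a covariate.**
- Variance of a change score: 2(1 − rho)
- Residual variance after baseline adjustment: 1 − rho² = (1 − rho)(1 + rho)
- Ratio of standard errors: sqrt(2/(1 + rho))

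| rho | SD of change | SD adjusted | SE ratio | Power for 0.5 SD, 30 per arm: change → adjusted |
|---|---|---|---|---|
| 0.3 | 1.183 | 0.954 | 1.240 | 37% → 53% |
| 0.5 | 1.000 | 0.866 | 1.155 | 49% → 61% |
| 0.7 | 0.775 | 0.714 | 1.085 | 70% → 77% |
| 0.9 | 0.447 | 0.436 | 1.026 | 99.1% → 99.3% |

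The ratio is never below 1. It does not depend on pooling, so the same large-sample factor applies to a separate 15-versus-15 analysis. The power column is illustrative only.

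**Step 2: leaving phase out of a pooled analysis.** With phases of equal size and arms balanced within them, the residual SD is multiplied by sqrt(1 + D²/4).
- D = 0: 1.000
- D = 0.5: sqrt(1.0625) = 1.031
- D = 1: sqrt(1.25) = 1.118
- D = 2: sqrt(2) = 1.414

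A constant acute-chronic difference in level cancels in the change score. Only a difference in change counts.

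**Step 3: simulation check** (4,000 runs, 15 per cell, rho = 0.7, effect 0.5 SD).
- Phases differ by 1 SD in level only: SE 0.199 for change with or without phase (power about 70% both ways) and 0.185 with baseline and phase. Ratio 0.199/0.185 = 1.076, close to the 1.085 of Step 1.
- Phases also differ in change by 1 SD of the outcome: SE 0.239 for change without phase, 0.199 for change with phase, 0.185 with baseline and phase. Power is 55%, 70% and 76%. In SDs of change, D = 1/0.775 = 1.29, and Step 2 predicts sqrt(1 + 1.29²/4) = 1.19; the simulation gives 0.239/0.199 = 1.20.
- Same setting with no true effect: rejection rate 2.0% for change without phase, against 4.8% with baseline and phase. The unadjusted test is conservative; it does not produce excess false positives.

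**The case against.** The strongest reply is that this reads too much into one general paragraph of a condensed article. The paragraph serves six different pilots, allows each to differ, excludes no covariate and gives no model formula. Parametric repeated-measures methods include mixed models, which can carry phase, and which recover the precision of baseline adjustment if the arms are constrained to a common baseline mean. The pilots are sized for finding usability problems, and effects are only to be explored. Much of this stands: it is why the point is conditional on the default being applied, and why its size is given as a range.

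Four stronger readings are tempting, and the documents support none of them.
- A reader might infer that acute and chronic patients will be pooled with phase ignored. The article says neither. If the phases are analysed separately, no pooled interval exists.
- A reader might infer randomisation stratified by phase. The article gives planned numbers within phase and says allocation is random, no more.
- A reader might conclude that baseline is ignored. It is used as a repeated level; the issue is how efficiently.
- A reader might conclude that power is lost or the intervals are wrong. No power is claimed, the loss from omitting phase can be zero, and a conservative interval is imprecise rather than biased.

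What survives is that the default stands unreplaced for this pilot, and that a more precise comparison is available from variables already recorded.

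**Conclusion.** The point holds as a conditional, modest gain in precision. If the default is applied to the centrifuge pilot, the between-arm standard error is wider than with baseline adjustment by about 15% at rho = 0.5, 8.5% at 0.7 and 2.6% at 0.9. If phases are also pooled without a phase term, a further 0% to about 12% is added as the difference in recovery goes from nil to 1 SD of change. These figures rest on assumed correlations and phase differences, equal SDs at the two visits, and large-sample formulas for a single follow-up visit. No stated figure in the article is wrong on this account.

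One matter comes first. The centrifuge section describes three arms, a comparison with standard of care, and healthy older adults. Its sample paragraph counts only SAHC and passive control, in stroke patients. No model can be fixed until these agree.

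**What to change.** 1. Reconcile, within the Short-Arm Human Centrifuge section, the arms and the place of the healthy older adults with the planned numbers.
2. Then add a short statement for this pilot: the randomised arms are compared at each post-baseline time with the outcome's baseline value as covariate; any analysis that combines acute and chronic patients includes phase as a factor; the arm-by-phase interaction is reported descriptively.
3. For skewed outcomes, use the same model on ranks, or a van Elteren test stratified by phase (this handles phase but not baseline).
4. Say whether acute and chronic patients will be combined or analysed separately.

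The cost is wording and about two degrees of freedom: with 60 patients in two arms, residual degrees of freedom go from 60 − 2 = 58 to 60 − 4 = 56. No new data are needed.

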#### Harmonization (Phase 3)

Via the Delphi method, the living labs will reach consensus on which procedures (ie, outcomes, outcome measures, and devices) to use in a rehabilitation context. Each outcome, outcome measure, and device will be represented as an item in a list. In Delphi survey round 1, the international panel of living lab experts will be instructed to rate the importance of each item and asked to provide new items or suggest revisions of existing items. Consensus will be reached when at least 70% of the panel strongly agree or disagree on inclusion or exclusion of an item. Items that did not reach agreement and newly suggested items will be taken to round 2, together with feedback of round 1 responses. After the second round, items will be ranked by importance, and a list of items will be created. This list will be distributed among the panel members to discuss during a final consensus meeting.

### Ethical and Legal Considerations

On a lower level, each partner institution involved in this study will submit an institutional review board application or ethical committee application according to the respective national regulations at the latest in February 2022. Informed consent will be obtained from all participants before data collection. For the pilot study involving individuals with (mild) cognitive disabilities, a team of trained psychologists will conduct recruitment of participants to ensure that potential participants’ cognitive functions and comprehension abilities allow them to provide written informed consent. Only pseudonymized data will be shared among the living labs in the context of harmonization of procedures and protocols.

On a higher level, with the VITALISE project, we also aim to collect information on differences and similarities concerning legal frameworks, data management, and privacy. To date, the following project deliverables have addressed the issues of legal frameworks, privacy, and data management: Deliverable *D1.2 First Version of Ethics and Safety Manual* (submitted to European Commission on September 29, 2021) reports on the VITALISE project’s international, European, and national ethical regulations, device standards, and certifications as well as accepted data management procedures; presents a first plan for the VITALISE scheduled data collection to be compliant with the reported regulations and guidelines; and evaluates potential concerns. In addition, project deliverable *D1.4 Data Management Plan (first version)* (submitted to European Commission on September 29, 2021) provides provisory information regarding the data to be collected during the project, addresses the issue of data reuse for further exploitation by expanding on the manner in which the data will be made accessible, and gives information on the data’s curation and preservation. Deliverables will be available to the general public via the VITALISE project website [1] after completion of the European Commission review process (approximately October 2022). Concerning informed consent procedures, identification and recruitment of participants, security measures, and anonymization or pseudonymization procedures of personal data and data transfer to non-EU countries, two project deliverables *D14.1 H—Requirement No. 1* and *14.2 Protection of Personal Data—Requirement No. 3* have been submitted to the European Commission on November 29, 2021. These deliverables will, however, only be available to the consortium members and Commission services.

## Results

Research activities (eg, participant enrollment, data collection, and data analysis) for this project will start in March 2022 (phase 1) and June 2022 (phase 2) and end in March 2024. Phase 1 (cocreation) will provide insights into different stakeholders’ views (ie, end users, clinicians, and informal caregivers) on the role of technology in rehabilitation on a European level (and beyond), as well as specific suggestions regarding rehabilitation innovations. Phase 2 (small-scale pilot studies) will provide insights into end user experiences, and usability and preliminary effectiveness of 6 selected neuropsychological or physical rehabilitation interventions for patients with stroke and older individuals. Phase 3 (harmonization via the Delphi methodology) will provide a consensus on harmonized screening, outcomes, and outcome measures for living lab research in the context of technology in rehabilitation. Together, these research activities will provide an opportunity for all involved living labs (and beyond) to gain knowledge on specific technologies intended for rehabilitation and to discuss and adopt each other’s technologies or procedures, to harmonize living lab procedures and infrastructures concerning the use of innovative technology in rehabilitation on a European level.

